Chronic suppressive therapy with valacyclovir is safe, well-tolerated and already in widespread use to prevent HSV outbreaks in those with frequent (five times a year or more) clinical reactivation. However, up to 90% of individuals with HSV-2 infection do not have any symptoms at all[53]. If HIV co-infected, such individuals may benefit from HSV-2 suppressive therapy not only through its effects on reducing herpes transmission and herpes reactivation, [54-56] but also through its salutary effects on HIV. The purpose of this multicentre, randomized, placebo-controlled clinical trial is therefore to answer the question, "Among adults co-infected with HIV and HSV-2 who are not using chronic suppressive anti-HSV therapy and who are neither currently using nor deemed to require HAART, can oral valacyclovir 500 mg twice daily delay the time until the need for HAART initiation?"

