### Study Objectives

The primary objective of this trial is to compare the time from enrolment to the primary endpoint of either a CD4 cell count ≤ 350 cells/mm^3 ^measured on two consecutive occasions at least 1 month apart, or initiation of HAART for any reason, between adults with both stable untreated HIV and HSV-2 co-infection who are randomized to valacyclovir compared to those randomized to placebo.

Secondary objectives are as follows:

• To compare the annual rate of change in the absolute CD4 cell count between study arms.

• To compare the annual rate of change in the CD4 cell count percentage between study arms.

• To compare the median log_10 _HIV viral load between study arms.

• To compare the rate of drug-related adverse events between study arms.

• To compare the median frequency of HSV reactivations per year between study arms.

• To compare the rate of acyclovir-resistant HSV between study arms.

• To compare quality of life between study arms.

A substudy will characterize plasma markers of inflammation in this cohort of HAART-naive HIV-infected patients and compare the levels of these markers between study arms.

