### Study Hypotheses

The primary hypothesis of the trial is that valacyclovir 500 mg orally twice daily will delay the time until HAART is initiated among adults co-infected by stable untreated HIV and HSV type 2 co-infection. The secondary hypotheses are that valacyclovir 500 mg orally twice daily is associated with a slower rate of change in both the absolute CD4 cell count and the CD4 cell count percentage, a lower median log_10 _HIV viral load, a similar rate of drug-related adverse events, a lower frequency of HSV reactivations, a similar rate of acyclovir-resistant HSV, and improvements in quality of life compared with placebo.

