### Secondary Analyses

Random effects models will be used to compare the annual rate of change in the absolute CD4 cell count, the annual rate of change in the CD4 cell count percentage, and the median log_10 _HIV viral load between study arms. The rate of drug-related adverse events per year of follow-up, the number of episodes of HSV reactivations per year occurring at any anatomic site, the proportion of microbiologically confirmed flares of HSV during the trial that are caused by laboratory-confirmed acyclovir-resistant HSV, and the median overall quality of life score [84] at each 6-monthly time point will be compared between groups using Wilcoxon rank sum tests. All analyses will be by intention to treat, meaning that all participants will be analysed in the groups to which they were randomized.

Efforts to ensure that the CD4 and other trial data are well collected include biannual investigator meetings to review study procedures, regular site monitoring visits, and electronic data checks at the CTN National Data Centre. Because the analyses on rates of change in CD4 will only include CD4 counts prior to HAART initiation, the usual problem in HIV clinical trials of missing data among patients doing poorly clinically and dropping out of the trial is not anticipated to be an issue. Patients doing poorly clinically will reach the primary outcome, and it is only their CD4 counts before this time that will be included in the analysis.

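### HSV reactivations: a median and a rank test on individual yearly rates suit a mostly-zero outcome with unequal follow-up badly; a person-time rate ratio is better

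*Protocol article*

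**What the plan says.** All references are to the protocol article.

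- Study Objectives lists as a secondary aim: "To compare the median frequency of HSV reactivations per year between study arms".
- Secondary Analyses defines the measure as "the number of episodes of HSV reactivations per year occurring at any anatomic site" and says that it, with several other outcomes, "will be compared between groups using Wilcoxon rank sum tests".
- Study Hypotheses expects "a similar rate of drug-related adverse events, a lower frequency of HSV reactivations" on valacyclovir.
- Background notes that "up to 90% of individuals with HSV-2 infection do not have any symptoms at all".
- Eligibility Criteria excludes people who used chronic anti-HSV therapy in the past 6 months or are expected to need it. Short episodic courses are allowed.
- Duration of Study Participation ends a participant's follow-up at the primary endpoint, or otherwise at the end of the 5-year study. The maximum is therefore 3 to 5 years, depending on entry date.

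For drug-related adverse events the wording differs. The objective is "To compare the rate of drug-related adverse events between study arms" and the analysis uses "The rate of drug-related adverse events per year of follow-up"; no median is mentioned.

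The article gives no expected flare rate, no expected adverse-event rate, and no power for either comparison.

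**The concern.** Three features of the HSV outcome fit the stated method badly.

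1. **Many zeros.** If more than half of each arm has no episode, the median yearly frequency is 0 in both arms whatever the drug does.
2. **Unequal follow-up.** One flare in 3 months is 4 per year and ranks above four flares in 4 years, which is 1 per year. The rank test gives both participants the same weight, although one rate rests on 16 times as much observation as the other.
3. **Follow-up related to treatment.** If valacyclovir delays the endpoint as hypothesised, that arm is watched longer and has more chance of a first, non-zero value. This works against the hypothesis of fewer flares.

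The trial's rationale runs from HSV suppression to lower HIV viral load to slower CD4 decline. Symptomatic reactivation is the one listed outcome that measures HSV suppression in every participant. If the primary result is null, readers will ask whether HSV was in fact suppressed, and an inefficient analysis could wrongly suggest that it was not. A rank test also gives no rate ratio to report.

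**Working it through.** The article gives no figure for this comparison to reproduce, so the check is of how the stated method behaves.

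**Inputs from the article.** 240 per arm; 2 years' accrual and a 5-year study; time to endpoint 2 versus 2.75 years; 25% loss, read here as loss by 3 years.

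**Assumptions.** Exponential times, with 2 and 2.75 years read as medians. A share p of participants is flare-prone, with a mean of 1 flare/year on placebo and gamma (shape 1) variation between them. Two-sided 5% test.

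**Step 1, follow-up.** Loss hazard −ln(0.75)/3 = 0.096 per year. Endpoint hazards ln2/2 = 0.347 and ln2/2.75 = 0.252. Total h = 0.4425 (placebo) and 0.348 (valacyclovir). With administrative censoring uniform on 3 to 5 years, mean follow-up = [1 − (e^(−3h) − e^(−5h))/(2h)]/h:
- placebo: (1 − 0.176)/0.4425 = 1.86 years
- valacyclovir: (1 − 0.254)/0.348 = 2.14 years

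On placebo, 1 − e^(−0.4425) = 36% leave within a year and e^(−1.3275) = 27% remain at 3 years. Follow-up is thus very uneven.

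**Step 2, the median.** With p of 40% or less, at least 60% of each arm is at zero, so the median is 0 in both arms whatever the effect. In simulation it was also 0 in both arms at p = 60%.

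**Step 3, why the rank test loses power (p = 20%, rate halved).** With most values tied at zero, the test mainly compares the share with any flare, p × (1 − E[1/(1+λT)]), where λ is the mean flare rate among the prone and T is follow-up:
- placebo (λ = 1): 0.2 × (1 − 0.448) = 11.0%
- valacyclovir (λ = 0.5): 0.2 × (1 − 0.550) = 9.0%
- SE = √(0.110×0.890/240 + 0.090×0.910/240) = 0.0274
- z = 0.020/0.0274 = 0.74; power ≈ Φ(0.74 − 1.96) ≈ 11%

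Halving the rate barely changes who has any flare, partly because the treated arm is observed longer.

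**Step 4, the person-time rate ratio in the same case.** Expected flares are 240×0.2×1.86 = 89 and 240×0.2×0.5×2.14 = 51. The between-person variance factor is (2p − p²)/p² = 9, and E[T²]/E[T]² = 1.54 and 1.45.
- Var(log ratio) = 1/89 + 1/51 + 9×(1.54 + 1.45)/240 = 0.143; SE = 0.378
- z = 0.693/0.378 = 1.83; power ≈ Φ(1.83 − 1.96) ≈ 45%

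**Step 5, simulation of the full tests.** Power, Wilcoxon versus rate ratio with robust variance. Ranges cover separate runs.

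| Flare-prone | Rate ratio 0.5 | Rate ratio 0.3 |
|---|---|---|
| 10% | – | 19-20% vs 63% |
| 20% | 12% vs 47-50% | 39-42% vs 87-90% |
| 40% | 29-31% vs 77-81% | 77-81% (Wilcoxon) |
| 60% | – | 97% (Wilcoxon) |

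**Step 6, other assumptions.** With 2 flares/year among the prone:
- Halved rate: 8% vs 30% (10% prone), 13% vs 53% (20%), 20% vs 74% (30%), 43% vs 93% (50%), 91% vs 99% (80%).
- 75% reduction: 22% vs 76%, 47% vs 98%, 72% vs 99%, 98% vs 100% and 100% vs 100% for the same shares.
- At 30% prone, the 20% Wilcoxon power for a halved rate rises to 29% if both arms have equal follow-up. The difference is the cost of the longer observation on valacyclovir.
- If everyone carries some risk (gamma shape 0.5, 0.1-1 flare/year): 42-84% vs 68-97% for a halving. Wilcoxon reaches 93-100% for a 75% reduction.

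**Step 7, type I error.** Wilcoxon rejected in 4-9% of null trials. The robust rate ratio rejected in about 5-7%, rising to 8% when 93% of values are zero, where some negative binomial fits also failed.

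**Step 8, adverse events.** For a doubled rate, from 0.05-0.5 per year on placebo, power was 71-96% (Wilcoxon) vs 63-97% (rate ratio). Wilcoxon shows no loss.

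**The case against.** The case for leaving the plan alone has real weight.

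- **The test is valid.** Wilcoxon compares distributions, not medians, and holds its type I error. For HSV the median appears only in the objective. This stands: the issue is efficiency and interpretability, not validity.
- **The flare-prone share is unknown.** The 90% figure is an upper bound for HSV-2 infected people in general, not an estimate for this cohort. The outcome counts reactivation at any anatomic site, HSV-1 co-infection is expected, and people who treat occasional flares remain eligible. If half or more are prone, or all carry some risk, large reductions are found by either method. This stands, so the power loss must be stated conditionally. A reader might infer that large effects will generally be missed; the article does not support that.
- **Other evidence of drug activity exists.** Pill counts, self-report, urine acyclovir and viral load are all collected. This is partly right: the first three show intake and viral load shows the HIV effect, but none shows HSV suppression.
- **The alternative is slightly liberal when flares are very rare.** True, so part of its advantage at 10% prone is inflated. At 20-40% prone its null rejection is close to nominal and the gap remains large.

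A reader might also extend the criticism to adverse events. The documents do not support that. They attach no median to adverse events, give no basis for assuming mostly zero values, and the check shows no power loss. What remains is that "a similar rate of drug-related adverse events" cannot be shown by a non-significant test, but the article does not say that non-significance will be read that way.

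**Conclusion.** The point holds for HSV reactivations. If most participants have no episode, which the article's own statements make plausible, the median frequency is uninformative and the rank test on individual yearly rates uses the data inefficiently. With an assumed 20-40% flare-prone at 1 flare a year, power for a halved rate is about 12-30% against about 47-80% for a person-time rate ratio. At 10-20% prone, a 70% reduction is missed in more than half of trials; at 60% prone it is detected by either method. These sizes rest on assumed flare rates, because the article gives none. The primary analysis is unaffected. This is a cheap, worthwhile improvement to a secondary analysis that helps to interpret the primary result. For adverse events, an estimate with its interval is a minor addition only.

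**What to change.** - In Secondary Analyses, take HSV reactivations out of the list of rank tests. Analyse each participant's episode count by negative binomial regression with log follow-up time as offset, and report the rate ratio with 95% CI. Name Poisson regression with robust variance as the fallback if the model does not converge.
- In Study Objectives, replace the median frequency with the rate of HSV reactivations per person-year.
- Optionally, report a rate ratio with 95% CI for drug-related adverse events too, and judge the similar-rate hypothesis from that interval.

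Cost: analysis wording only. Episode counts and follow-up times are already collected. The downside is a model assumption, and slightly liberal robust errors (about 7-8% null rejection at a nominal 5%) if flares prove very rare. The change should be made before unblinding.

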### Randomization and blinding methods

Randomization is stratified by site in permuted blocks of variable size (4 and 6) using a computer-generated list of random numbers. The CTN created and coordinated the allocation sequence, and randomization is performed through a secure website which ensures allocation concealment. All participants and study personnel (including investigators, research coordinators, data analysts) will be blinded to treatment allocation throughout the trial. Access to the allocation code will be restricted to one study statistician who will not perform the final study analyses.

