### Outcome Measures

The primary outcome is the time from baseline until reaching the primary endpoint, a composite of either a CD4 cell count ≤ 350 cells/mm^3 ^measured on two consecutive occasions at least 1 month apart, or initiation of HAART for any reason, whichever occurs first. This endpoint was selected because reaching the treatment threshold for initiating HAART is an important clinical event signifying the need for lifelong therapy. The CD4 count of ≤ 350 cells/mm^3 ^must be confirmed by a second measurement to verify the CD4 count is within the treatment range before initiating therapy. The primary endpoint also includes the initiation of HAART for any reason, since patients who start HAART outside these guidelines are also committed to lifelong therapy. This group may include individuals who choose to start therapy at earlier stages of disease (e.g. because of high viral load set-point), and some who develop HIV-related complications (e.g. tuberculosis) at higher CD4 cell counts, among others. For example, women who initiate HAART during pregnancy primarily for the prevention of mother-to-child transmission of HIV, and hepatitis B co-infected individuals who initiate HAART primarily for the purposes of treating their hepatitis B infection, will also be considered to have met the primary endpoint. It was important not to restrict the primary endpoint to initiation of HAART alone, since some patients may not initiate HAART despite reaching treatment thresholds for reasons including patient anxiety, concerns about adherence, and lack of familiarity with guidelines[65].

HAART initiation guidelines are continuously under evaluation, and HIV treatment guidelines may change. However, a change will not threaten the integrity of the study for a number of reasons. First, guidelines on HAART initiation have recently been revised[6,9]. Recommendations to uniformly increase the treatment threshold above 350 cells/mm^3 ^in both industrialized and middle-income settings based on definitive clinical trial data are not anticipated during the course of the trial. Second, as described above, the primary endpoint of this study is a composite of not only meeting the current CD4 threshold of 350 cells/mm^3^, but also the initiation of HAART for any reason, whichever occurs first. Finally, randomization in this trial will be stratified by site to help account for variation in practice regarding initiation of HAART across sites.

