### Sample Size Calculation

It is hypothesized that suppression of HSV-2 using valacyclovir will increase the time until participants' CD4 counts reach ≤ 350 cells/mm^3 ^or initiate HAART from the expected value of 2 years to 2.75 years (see justification below). Participants will be recruited over 2 years and followed over 3 years. Using a conservative estimate that 25% of the sample will be lost to follow-up on average half way through the 3-year follow-up period, the expected years of follow-up is 0.75 × 3 years + 0.25 × 1.5 years = 2.625 years overall. In order to detect a difference of 0.75 years with a two-sided α = 0.0492 (adjusted for multiple analyses by the method of O'Brien and Fleming)[70] and 80% power in a survival analysis, 240 individuals will be required in each study arm, or 480 participants overall[71].

The expected rate at which HIV disease would progress in HAART-untreated individuals was based on both a retrospective review of patient charts and the published literature. Among 142 patients with at least 3 CD4 counts before starting HAART, with baseline CD4 count > 400 cells/mm^3 ^at the Toronto General Hospital Immunodeficiency Clinic, the median time from first presentation to reaching CD4 ≤ 350 cells/mm^3 ^was 2.0 years ([name], [name]: personal communication). In the subset with higher baseline CD4 counts (> 500 cells/mm^3^), the median time was 2.5 years. Consistent with these findings, a published retrospective observational cohort study of 4268 HIV-infected individuals in the United Kingdom with baseline CD4 counts > 500 cells/mm^3 ^also found the median time to until reaching CD4 counts ≤ 350 cells/mm^3 ^or initiation of antiretroviral therapy was 2.5 years[72]. Both are consistent with the generally accepted rate of CD4 count decline of 50-60 cells/mm^3 ^per year[2,3].

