### Primary Analysis

The primary outcome of the trial is the time from baseline until reaching the primary endpoint, a composite of either a CD4 cell count ≤ 350 cells/mm^3 ^measured on two consecutive occasions at least 1 month apart, or initiation of HAART for any reason, whichever occurs first. The primary analysis will be a proportional hazards model, stratified by site, which will estimate the relative risk of progression to this endpoint associated with valacyclovir. Participants who do not reach either endpoint will be censored at the date of last CD4 count. The primary analysis will be conducted at the conclusion of the trial using the α = 0.0492 level of significance. This significance level adjusts for one interim analysis of the data according to the method of O'Brien and Fleming[70].

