### Subgroup Analyses

Three sets of subgroup analyses of the primary outcome will be performed. First, analysis will be conducted according to serological evidence of dual HSV-2 and HSV-1 infection, compared with only HSV-2 infection. These exploratory data will contribute to the emerging literature on the prognostic significance of HSV-1 in HIV co-infection[85]. Second, subgroup analyses will also be performed to determine whether participants with higher levels of adherence achieve greater benefits than those with lower adherence, recognizing that such associations may be partially driven by unmeasured confounders such as health-seeking behaviours. Third, subgroup analyses will also be performed according to country (Canada vs Brazil vs Argentina) since small differences related to clinical practice patterns, gender mix, clade or unknown factors may exist.

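### Four secondary outcomes are compared by unstratified Wilcoxon tests although randomisation and the primary model are stratified by site; the tests are conservative if site matters (minor, cheap to improve)

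*Protocol article*

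**What the plan says.** Randomization and blinding methods: "Randomization is stratified by site in permuted blocks of variable size (4 and 6". Outcome Measures gives the reason: randomisation is "stratified by site to help account for variation in practice regarding initiation of HAART across sites". Primary Analysis follows the design: "The primary analysis will be a proportional hazards model, stratified by site".

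Secondary Analyses names two sets of methods. The first covers CD4 count, CD4 percentage and viral load: "Random effects models will be used to compare the annual rate of change in the absolute CD4 cell count" and the other two measures, with no list of model terms. The second covers the yearly rate of drug-related adverse events, the yearly number of HSV reactivations, the proportion of confirmed flares that are acyclovir-resistant, and the six-monthly quality of life score. These "will be compared between groups using Wilcoxon rank sum tests". Site is not mentioned for that test.

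Subgroup Analyses, on country comparisons of the primary outcome, says that "small differences related to clinical practice patterns, gender mix, clade or unknown factors may exist".

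**The concern.** The article says stratified where it means stratified, and in the second set it names the ordinary two-sample test. So this is a stated method, not a detail held over for the analysis plan.

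When allocation is blocked within site, the arms are nearly balanced in every site, and differences between sites largely cancel from the arm comparison. A test that pools all participants still includes those differences in its reference variance. It then rejects less often than its nominal level.

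Two consequences follow. For HSV reactivations and quality of life, where Study Hypotheses expects a benefit, some sensitivity may be given up. For adverse events and resistant HSV, where it expects similar rates, a test that under-rejects makes the hoped-for non-significant result slightly easier to obtain.

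Site differences are plausible for some of these outcomes. Quality of life is self-reported in three countries, and flares are sampled for confirmation only where resources allow, which bears on the resistance proportion.

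**Working it through.** **The plan's own figure.** No power or error rate is stated for the secondary tests. The only figure to reproduce is the primary sample size, "240 individuals will be required in each study arm, or 480 participants overall", at "two-sided α = 0.0492" and 80% power. With hazard ratio 2/2.75 = 0.727, the Schoenfeld formula gives 4 × (1.967 + 0.842)² / (ln 0.727)² ≈ 312 events. Taking 2 and 2.75 years as exponential medians, uniform accrual over 2 years and then 2.625 years of follow-up, the event probability is 0.652, so N = 312/0.652 ≈ 479. This reading is not unique, but it reproduces 480. Nothing in it depends on the secondary tests.

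**Large-sample size of the effect.** Let r be the share of an outcome's variance explained by site. The documents give no value, so r is assumed over a range. With perfect balance within site:

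- true standard error = √(1 − r) × the standard error that the plain test uses;
- real alpha = 2 × [1 − Φ(1.96/√(1 − r))];
- power of the plain test when the stratified test has 80% = Φ(2.80 − 1.96/√(1 − r)).

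| r | SE overstated by | Real alpha | Power of plain test |
|---|---|---|---|
| 0.05 | 2.6% | 0.044 | 78.5% |
| 0.10 | 5.4% | 0.039 | 76.9% |
| 0.20 | 11.8% | 0.028 | 72.9% |

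For example, at r = 0.10: 1/√0.90 = 1.054, 1.96 × 1.054 = 2.066, and 2 × [1 − Φ(2.066)] = 0.039.

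**Check under the actual block scheme.** The formula charges nothing for incomplete blocks or for stratifying over small sites. A simulation does: 480 participants, site-stratified blocks of 4 and 6, a normal outcome, complete data, two-sided 0.05, and both tests applied to the same data sets. The number and size of participating sites are not given, so three layouts were assumed: 12 equal sites, 20 unequal sites, and 30 sites of which 28 are small. The shift of 0.262 SD gives the plain test about 80% power when site has no effect. Each cell used 4,000 null runs and 2,500 power runs (Monte Carlo standard errors about 0.35 and 0.8 percentage points).

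| Site share | Type I error, plain test | Power, stratified minus plain (points) |
|---|---|---|
| 0 | 0.048 to 0.051 | −0.6 to −2.5 |
| 0.01 | 0.050 to 0.052 | −1.0 to −1.4 |
| 0.05 | 0.043 to 0.051 | −1.7 to +0.5 |
| 0.10 | 0.039 to 0.045 | +0.2 to +2.0 |
| 0.20 | 0.031 to 0.033 | +2.6 to +4.0 |
| 0.30 (first two layouts only) | 0.025 | +6.4 |

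The site-stratified test stayed between 0.047 and 0.055 in every cell. The alpha results agree with the formula. The power gain is smaller than the formula suggests, partly because the two calculations set 80% power on different tests and partly because small strata cost something.

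**The case against.** The strongest reply is that this is harmless. The tests err on the safe side, the outcomes are secondary with no stated power, and the stated reason for stratifying is variation in HAART initiation, which bears directly on the primary endpoint and is handled there. The article itself calls country differences small. All of that stands, and it limits the point to a minor one.

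The remedy also has limits. Where site has little influence, stratifying over many small sites loses a little power. The resistance proportion exists only for participants with confirmed flares, in a setting where the article puts asymptomatic HSV-2 at up to 90% and resistance at 5-6%. Split by site, most strata would carry no information.

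Three stronger readings are tempting and are not supported:

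- *The error rates are invalid.* In no case examined was type I error materially above nominal; the departure is towards caution.
- *Power is thrown away for nothing.* That depends on an unknown site effect; below about 10% of the variance there is little or nothing to gain.
- *The random effects models also ignore site.* The article lists none of their terms, so site is neither in nor out, and listing terms is properly left to the analysis plan.

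**Conclusion.** The point holds for the Wilcoxon tests only, and it is minor. As named, they do not follow the site-stratified design that the primary model follows. They are conservative to the extent that site matters: real alpha about 0.04 at a site share of 10% and about 0.03 at 20%, with negligible effect at 5% or less. The gain in power from stratifying is at most about 2 points at 10% and 3 to 4 points at 20%.

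These sizes rest on assumed variance shares, assumed site layouts, a nominal 0.05 for the secondary tests and a normal outcome. Adverse event and reactivation rates will have many ties, so the figures are less certain there and fit quality of life best. The primary analysis, its alpha and the 480 participants are untouched.

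**What to change.** In Secondary Analyses, replace the plain rank sum tests for quality of life, HSV reactivations and adverse event rate with site-stratified (van Elteren) versions. Pool very small sites, for example within country, by a rule fixed before unblinding. For the resistance proportion, stratify by country at most. If the analysis plan already says this, only the article's wording differs and no further change is needed.

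The cost is one sentence and a pooling rule, with no new data. The downside is about 1 to 2.5 points of power if site effects turn out absent or weak and small sites are not pooled; the largest loss in the simulation was in the layout with 28 small sites, which is the situation that pooling addresses.

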### Duration of Study Participation

Study visits will occur every 3 months over 2 years of participant accrual and 3 years of follow-up. Once enrolled, participants will enter the follow-up period during which they will be treated with either valacyclovir or placebo, and undergo follow-up visits every 3 months. Follow-up for an individual participant will continue until the end of the 5-year study period unless the primary endpoint is reached first. This means that all participants will be followed until the 5-year trial ends, unless they reach a primary endpoint first.

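### The CD4-slope analysis is given two different cut-offs, and one of them, read literally, leaves out the low counts that stop follow-up and so flattens the slopes and shrinks the arm difference

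*Protocol article*

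**What the plan says.** Secondary Analyses names random effects models for the annual change in absolute CD4 count and CD4 percentage. It then states an inclusion rule: "the analyses on rates of change in CD4 will only include CD4 counts prior to HAART initiation". From this it concludes that "missing data among patients doing poorly clinically and dropping out of the trial is not anticipated to be an issue". The supporting sentence uses a different cut-off, the primary outcome: "it is only their CD4 counts before this time that will be included in the analysis".

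Primary Analysis defines the CD4 part of the endpoint as a count ≤350 "measured on two consecutive occasions at least 1 month apart, or initiation of HAART for any reason, whichever occurs first". Outcome Measures says the first low count has to be confirmed by a second. Neither section says which of the two counts dates the event. Under Duration of Study Participation, a participant is followed to the end of the five-year study "unless the primary endpoint is reached first".

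**The concern.** The two cut-offs differ for every participant whose endpoint is reached on CD4 and who is not yet on HAART. Outcome Measures expects such participants: the composite was chosen partly because some patients pass the threshold without starting treatment. For them, one rule keeps the qualifying counts and the other, taken literally, drops one or both. An analyst cannot follow both.

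The choice matters because the CD4 value itself ends follow-up. A likelihood-based random effects model copes with that when the values that triggered stopping are in the data, since the missing later counts then depend only on observed ones (missing at random). If the triggering value is removed, that protection goes.

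The deletion is also one-sided. Among participants with a first count ≤350, those whose repeat is above 350 keep the repeat, and those whose repeat is ≤350 lose it. Low repeats go and high repeats stay, so declines look too shallow, more so in the arm that declines faster.

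At stake is the first secondary objective, which tests the step on which the trial's effect size rests: a slowing of decline by 10 cells/mm³/year (Sample Size Calculation).

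**Working it through.** **The plan's own figure.** The documents give no figure for the slope analysis. The primary sample size reproduces and is not in question. With exponential medians of 2 and 2.75 years, HR = 2/2.75 = 0.727. Events = 4(1.967 + 0.842)²/(ln 0.727)², which rounds up to 312. Uniform two-year accrual plus 2.625 years of follow-up gives an average event probability of 0.652. Then 312/0.652/2 ≈ 239 per arm, against 240 stated.

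**Inputs from the article.**
- Decline without treatment 50–60 cells/year (55 used) and expected arm difference 10, so true slopes are −55 and −45 (Sample Size Calculation).
- Entry CD4 400–900 on two occasions (Eligibility Criteria).
- Visits every 3 months, follow-up ending at the endpoint (Duration of Study Participation).
- Endpoint of two consecutive counts ≤350 (Primary Analysis).

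**Assumptions, not in the documents.** Entry CD4 mean 560, SD 100; between-person slope SD 25–75 cells/year; within-person SD 50–110; other HAART starts 0 or 10% a year; confirming count 1 or 3 months after the first; loss 8% a year. The loss rate is close to the plan's 25% over 3 years, which is 1 − 0.75^(1/3) ≈ 9% a year.

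**Method.** Linear CD4 trajectories were simulated with the stopping rule (4,000–20,000 per arm per run) and fitted by maximum likelihood with random intercept and slope. The same simulated participants were analysed under each cut. Attenuation = 1 − estimated difference/10.

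**Central case** (slope SD 50, within-person SD 80, no other HAART starts, no eligibility truncation):

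| Counts kept | Placebo slope | Valacyclovir slope | Difference | Attenuation |
|---|---|---|---|---|
| No stopping at the CD4 endpoint (reference) | −54.6 | −44.6 | 9.9 | 1% |
| All, including both qualifying counts | −54.4 | −44.5 | 9.9 | 1% |
| Confirming count dropped | −46.6 | −37.8 | 8.8 | 12% |
| Both counts ≤350 dropped | −34.5 | −27.4 | 7.1 | 29% |

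Dropping the confirming count flattens placebo by 54.4 − 46.6 = 7.8 and valacyclovir by 44.5 − 37.8 = 6.7. The difference loses 7.8 − 6.7 = 1.1. Dropping both flattens them by 19.9 and 17.1, so it loses 2.8. With eligibility truncation added, the three differences are 10.0, 9.2 and 7.9.

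**Range over all settings.**
- Both kept: difference 9.5–10.3.
- Confirming count dropped: 8.7–9.6 (about 5–13% too small), placebo slope −44 to −53.
- Both dropped: 6.9–8.6 (about 14–31% too small), placebo slope −28 to −49.

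**A second set of assumptions.** Entry mean 470–550, placebo slope −55 or −80, slope SD 30–60, within-person SD 50–90, other HAART starts 2–15% a year, loss about 9% a year. Results: within about 5% of truth with both counts kept, 4–14% too small without the confirming count, 16–38% too small without either. In one setting (true difference 10.4, true placebo slope −55) the estimates were 10.4 and −58, then 9.3 and −51, then 7.5 and −41.

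**Combined.** 4–14% if one count is lost, 14–38% if both are.

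**Against sampling error.** In the central case, the standard error of the difference at 240 per arm is about 5.6, 5.3 and 4.9 under the three cuts. The expected z is 9.9/5.6 = 1.77, 8.8/5.3 = 1.66 and 7.1/4.9 = 1.45. Some power is lost, though each shift is smaller than one standard error.

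**The case against.** The best defence is that the rule is the sentence naming HAART initiation, and that the later sentence only explains, loosely, why dropout should not matter. Under the HAART rule the qualifying counts stay in, and the simulations show no material bias. That stands in part: a reader might infer that the plan is settled on discarding the counts ≤350, and the text does not support that. What it does support is that two stated rules conflict and that one of them, as written, is harmful.

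Second, follow-up ends at the endpoint, so the rules differ by only one or two counts per participant. This is true, but those are the counts that decide whether stopping is ignorable.

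Third, a reader might take the larger loss as the expected one. It requires dating the endpoint at the first count ≤350, which the article does not say. The confirmation requirement makes the second count at least as natural a date, and then the smaller range applies.

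Fourth, a reader might set the sample-size assumption that "25% of the sample will be lost to follow-up on average half way through the 3-year follow-up period" against the missing-data assurance. The two do not contradict each other. The assurance concerns patients doing poorly, and the 25% is a planning allowance with no stated link to CD4.

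Finally, a sensitivity analysis modelling CD4 jointly with dropout is a preference that an article may leave to the SAP. It is not part of this point.

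**Conclusion.** The point holds as an inconsistency with a harmful branch. Secondary Analyses states two cut-offs. The one tied to the primary outcome, read literally, omits at least the confirming count ≤350, makes the stopping informative, and biases both slopes and the arm difference toward zero. The difference is about 4–14% too small with one count lost, and about 14–38% too small with both lost. The direction was the same in every setting. The sizes rest on assumed variances, linear trajectories, and HAART starts and losses occurring at constant rates.

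The assurance about missing data does not follow from its stated reason: cutting the data before an outcome-driven stop creates informative missingness.

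The reach is limited. With no treatment effect, the same deletion acts equally in both arms and the difference stays centred on zero, so type I error is not at issue. The primary analysis and sample size are untouched. The cost is a diluted secondary estimate, some power, and absolute slopes that look too flat beside the 50–60 cells/year benchmark. Only absolute CD4 was simulated, so no size is claimed for CD4 percentage.

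**What to change.** State one cut-off: all CD4 measurements, absolute and percentage, taken before HAART initiation or up to the last visit, explicitly including both counts ≤350 that define the endpoint, in the likelihood-based random effects model.

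Delete the sentence limiting the data to counts before the primary outcome. Replace the assurance with a statement that stopping on CD4 is handled under missing at random because the triggering counts are included. That justification is exact for the absolute count, which is what triggers stopping. For percentage, use the same cut-off but make the claim more cautiously.

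This is a change of wording only. The counts are already collected to establish the endpoint, and keeping them has no downside.
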